### Randomization

Randomization will be by permuted blocks of varying size and stratified by diagnosis of *Diabetes mellitus*. Two randomization lists, one for each stratum, will be generated from the *randomization*.*com* website [18]. From the randomization lists, two sets of sequentially numbered opaque envelopes will be created, containing the identification of the trial groups. As the nutritional intervention will be tailored to the treatment group, there is no possibility of blinding.

### Nutritional intervention

Participants randomized to the intervention group will be subjected to an individualized nutritional intervention prescribed after 60 days of KTx by a professional nutritionist participating in the research through an individualized plan with a two-option substitution rate calculated with the aid of the *Virtual Nutri Plus 2*.*0* software, using nutritional recommendations for the late post-KTx period, according to Table 2 [10, 11]. The foods and preparations on the plan will be presented in the form of weights and conventional homemade measures [19, 20] that the patients are familiar with in their routines. In order to gain a better understanding of the diet plan, photographic records of portions of food [21] and real-sized food models made of silicone will be used as illustrations for demonstrating the portions suggested in the menu.

**Table 2 pone.0272484.t002:** Nutritional recommendations for food planning in the late post-KTx period.

Nutrient	Nutritional recommendation
Energy	25–30 kcal/kg/day
Protein	1.0 g/kg
Total lipids	< 30% of the total kcal
Saturated fatty acids	< 10% of total calories
Monounsaturated fatty acids	10–15% of total calories
Polyunsaturated fatty acids	≥ 10% of total calories
Cholesterol	< 300mg
Carbohydrates	50% of total kcal
Fiber	25–30 g
Sodium	3–4 g
Potassium	Restricted (1–3g) only if hyperkalemia and/or oliguria are present
Phosphorus	1200–1500 mg
Calcium	800–1500 mg
Iron	The need for supplementation depends on the body reserves
Magnesium	Supplementation, if required, while using cyclosporine
Water-soluble vitamins	Usually no need for supplementation
Vitamin D3	1 a 2 μg, if required

Source: Martins; Pecoits-Filho; Riella [10]. Riella; Martins [11].

Patients randomized to the control group will receive nutritional guidance for the post-transplant period as offered by the hospital. The guidelines manual will be prepared based on literature [10, 11] and will have information and suggestions for weight and blood lipid and glucose control, attention to the intake of foods that are sources of fat, sodium and general guidelines on healthy, safe eating and food recipes.

### Treatment adherence

Patients who receive the nutritional intervention will be followed up in the same period as the patients in the control group, with adherence to the food plan being verified through a 3-day food record (applied during all evaluation periods) for the evaluation of food consumption. In addition, the frequency of individuals in face-to-face consultations will also be assessed during these meetings, and the difficulties and doubts of patients about the diet plan will be addressed.

Patients, who during the course of the clinical trial, have the introduction of mammalian target of rapamycin (mTOR) inhibitors (everolimus or sirolimus) in their immunosuppressive regimen, initiate a protein food supplementation, or who abandon and withdraw the consent to participate will have their trial prematurely terminated.

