## Materials and methods

This is a single center, stratified and randomized clinical trial to evaluate the efficacy of individualized nutritional intervention considering normal protein diet with consumption of 1.0 g/kg versus standard nutritional guidelines in chronic kidney disease patients submitted to KTx in the previous two months. The trial site will be the Onofre Lopes University Hospital/Federal University of Rio Grande do Norte (UFRN), Rio Grande do Norte, Brazil.

The study was submitted to and approved by the Research Ethics Committee of Onofre Lopes University Hospital/UFRN with authorization number 3,127,266 and registered with the CAAE: 02445018.7.0000.5292. Eligible patients will be informed verbally and in written about the objectives, procedures and potential risks of the study. Those agreeing to participate will be asked to sign an informed consent form. The clinical trial was registered on the *Brazilian Clinical Trials Registry (REBEC)* online platform, obtaining the registration RBR-8XBQK5 and UTN (*Universal Trial Number*) U1111-1231-6000, linked to the World Health Organization (WHO).

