### Statistical analysis

The study will be analyzed by the modified intention-to-treat method, whereby all randomized patients who had at least one post-baseline measurement of proteinuria will be included in the primary analysis population. Data will be presented descriptively by means and standard deviations, or with absolute and relative frequencies, according to the respective scale of measurement. The difference between the groups in the change from baseline in the primary efficacy variable will be tested by analysis of covariance with a multiple linear regression model, with the baseline value entered as covariate, *Diabetes mellitus* entered as stratification variable, and study group as independent variable. For secondary efficacy variables, in those measured in an interval scale, the change from baseline will be compared between groups with the same method. For those variables that are related to patient sex (e.g., WC, sarcopenia), sex will be included as independent variable. For variables measured in ordinal scales, only the values observed in the last valid observation will be considered and will be compared between groups with the Wilcoxon-Mann-Whitney U test. No multiplicity correction of p-values will be applied to the secondary variables.

Statistical analyses will be performed using Stata 15.1 (Stata Corp., Collegue Station, TX). Tests with two-sided p values < 0.05 will be considered statistically significant.

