Furthermore, research indicates that post-KTx proteinuria can be controlled through the diet [40]. A nutritional intervention to control protein intake could contribute to reduce the overload of protein levels in the glomerular capillaries and renal tubules [41–45]. As a result, hyperfiltration and glomerular pressure decrease, reducing the urinary protein excretion rate [44, 45].

Therefore, as the reduction in proteinuria may favor better kidney function, as well as a longer graft survival and reduced mortality, the present study will use proteinuria as a primary efficacy variable in order to assess whether the intervention individualized nutrition may have an antiproteinuric effect post-KTx. And, thus, assess whether the patient can benefit in guaranteeing the success of KTx and a better quality of life.

The present clinical trial was concerned with outlining exclusion criteria that could be possible biases in the assessment of the benefit of individualized nutritional intervention in the management of proteinuria in the late post-KTx period. Among the exclusion criteria are focal segmental glomerulosclerosis, systemic lupus erythematosus and IgA nephropathy, which are underlying diseases recognized for developing recurrent proteinuria after KTx due to deposition of immune complexes in the kidneys that lead to progressive renal failure [46–48]; multiple organ transplantation and a history of recurrent transplantation due to chronic rejection that may increase the risk of kidney injury and lower graft survival [49, 50]; immunosuppressive therapy with mammalian target of rapamycin (mTOR) inhibitors (everolimus or sirolimus) which has proteinuria as an adverse effect [51, 52]; and hospitalization after KTx longer than 60 days, as it is associated with complications that can lead to lower survival and graft loss [53, 54].

One of the possible limitations of this protocol will be the impossibility of blinding, which may imply risks of bias. To reduce these risks, in this study, standardized measurements and tests of anthropometric assessments, quality of life and laboratory tests will be adopted. In addition, to reduce the potential for confounding due to the variability of the measures evaluated, the same nutritionist will carry out the nutritional intervention protocol.

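### Ending the trial of patients who start an mTOR inhibitor or a protein supplement stops proteinuria measurement after outcome- or treatment-linked events, which conflicts with the modified ITT analysis

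*Protocol article*

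**What the plan says.** In the Protocol article, the Treatment adherence section lists what ends a patient's trial. It covers patients who "have the introduction of mammalian target of rapamycin (mTOR) inhibitors (everolimus or sirolimus) in their immunosuppressive regimen" and those who "initiate a protein food supplementation, or who abandon and withdraw the consent to participate will have their trial prematurely terminated". Withdrawal of consent therefore stands on the same footing as two treatment events after which a consenting patient could still be measured. No other section of the article keeps such patients in follow-up.

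Three further statements bear on what these events mean:

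- The Discussion justifies an entry exclusion by pointing to "mammalian target of rapamycin (mTOR) inhibitors (everolimus or sirolimus) which has proteinuria as an adverse effect".
- Materials and methods describes the comparison as "individualized nutritional intervention considering normal protein diet with consumption of 1.0 g/kg versus standard nutritional guidelines".
- Randomization concedes that "there is no possibility of blinding".

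The Statistical analysis section begins "The study will be analyzed by the modified intention-to-treat method" and defines the set: "all randomized patients who had at least one post-baseline measurement of proteinuria will be included in the primary analysis population". ACR is due at T0, T3, T6, T9 and T12 (Evaluation and analysis of biochemical parameters). The 3-day food records kept by all patients already capture supplement use (Assessment of dietary intake).

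**The concern.** Excluding mTOR inhibitor users at entry is legitimate because it happens before randomisation. Applying the same criterion afterwards makes the available outcome data depend on something that happened during the trial. Here one event raises the primary outcome, by the article's own account, and the other changes the exposure under test.

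The supplement trigger is also unlikely to mean the same thing in both arms. The intervention arm has a protein target. The description of the control manual names none, although the manual draws on the same references. With open allocation, the decision to start a supplement, or to report one, could differ by arm.

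The planned analysis cannot recover an effect irrespective of these events without assumptions that the data cannot check, because post-event ACR is never collected. Ordinal secondary outcomes are affected too: they use each patient's final valid value, and termination moves that value to an earlier visit.

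**Working it through.** **1. The plan's own figure.** Inputs from Sample size and recruitment: mean log proteinuria 2.36, SD 1.55, α 0.05 (two-sided, from Statistical analysis), power 70%, 87 per group, 5% drop-out before the first follow-up visit.

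- Difference taken as 25% of the mean log value: 0.25 × 2.36 = 0.59.
- n = 2 × (1.960 + 0.524)² × 1.55² / 0.59² ≈ 85.2, so 86 per group. The t-test version gives 86.2, so 87.
- 87 / 0.95 = 91.6, so 92.

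The stated 87 and 92 reproduce, but only with 0.59. A 25% reduction in the geometric mean, which is how the text describes the target, is ln(1/0.75) = 0.288 on the natural-log scale. Both denominators are therefore shown below. The article does not give the base of the log; natural log is assumed.

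**2. Who is lost, and how.**

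| Time of event | Consequence under the two sections read together |
|---|---|
| Before T3 | No post-baseline ACR, so not in the modified ITT set |
| After T3 | In the set, with pre-event values only |
| Poor adherence alone | Not a termination event; measurement continues |
| Consent withdrawn | Measurement unavoidably ends |

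**3. Size of a possible shift.** Let q be the proportion terminated in an arm and s the log difference between the terminated and the remaining patients. The mean of those remaining is the full-arm mean minus q × s. With the same s in both arms, the group contrast shifts by (difference in q) × s. The same formula applies if pre-event values stand in for later ones, with s as the log rise after the event. The article gives neither q nor s, so these are assumptions:

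| Arm difference in q | ACR ratio | Shift (ln units) | Share of 0.288 | Share of 0.59 |
|---|---|---|---|---|
| 0.05 | 2 | 0.05 × ln 2 = 0.035 | 12% | 6% |
| 0.08 | 2 | 0.08 × ln 2 = 0.055 | 19% | 9% |
| 0.10 | 3 | 0.10 × ln 3 = 0.110 | 38% | 19% |
| 0 (same s) | any | 0 | 0% | 0% |

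The sign depends on which arm has more events.

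**4. A second illustration, on the SD scale.** Assume no true effect, 92 per group, 15% removed in one arm and 5% in the other, and removed patients 0.5 to 1 SD (0.78 to 1.55) higher. The shift is 0.10 × 0.78 to 0.10 × 1.55, that is 0.08 to 0.16, or 13-26% of 0.59. With SE = 1.55 × √(1/78.2 + 1/87.4) = 0.241, the two-sided type I error rises from 5% to about 6-10%.

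**5. Precision.** The 5% allowance covers only loss before the first follow-up visit. At a difference of 0.59 and 92 per group, total loss of 5%, 10% or 20% gives power of 71.1%, 68.8% or 63.7%. This is a modest cost; selection matters more.

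**The case against.** The strongest defence is that the rule has a stated rationale. Everolimus and sirolimus users are excluded because these drugs cause proteinuria, and the effect of the diet in the absence of drug-induced proteinuria is a recognised question. For that question post-event ACR is not the target value, and a higher ACR caused by the drug counts as bias only if the question is the effect as randomised. This stands, but it argues for collecting the data rather than against it: with post-event values in hand both questions can be answered, and without them only one can.

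It is also fair that no imbalance is shown. Nothing in the article says that the diet changes who is switched to an mTOR inhibitor; an arm difference is more plausible for supplements. Every rate used above is assumed.

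A reader might infer more than the text supports:

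- That the rule undoes the intention-to-treat comparison. It does not. Anyone with a T3 value stays in the set.
- That later visits compare only compliers. Non-adherence ends nobody's trial; it is monitored with food records and discussed at visits.
- That abandoning the diet plan is a separate trigger. The wording is best read as one event, abandonment together with withdrawal of consent.
- That no missing-at-random model could help. This is unproven; earlier ACR values might reduce the bias, and for the alternative question such a model might suffice.

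**Conclusion.** The concern holds in a limited form. The rule is stated outright, so it is not a detail left to an unseen analysis plan. It stops primary-outcome measurement in consenting patients after two events linked to the outcome or to the treatment, and this conflicts with a modified ITT analysis.

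Whether bias results depends on the events differing between arms in frequency or prognosis, which the article neither shows nor excludes. Under the assumed ranges the shift is small to moderate relative to the effect sought, in either direction. Should-fix, with moderate confidence.

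**What to change.** Reconcile Treatment adherence with Statistical analysis:

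- In Treatment adherence, separate the start of an mTOR inhibitor or a protein supplement from withdrawal of consent. Record the date and type of each as an intercurrent event, by arm.
- Continue ACR and secondary outcome measurement at the scheduled visits up to T12 in everyone who has not withdrawn consent.
- In Statistical analysis, use all these values as randomised in the primary modified ITT analysis. Add a sensitivity analysis that censors at either event.

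The change concerns measurement and analysis only; no change to clinical care is implied.

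The cost is low, since the visits, assays and food records are already planned, but it is not nil. The primary contrast will include the effects of mTOR inhibitors and supplements, which the sensitivity analysis addresses. Trial status gives recruitment as running from May 2019 to December 2022, so an amendment is needed mid-trial. Later values of patients already terminated may not be recoverable; their number should be reported by arm.

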### Evaluation and analysis of biochemical parameters

The urinary albumin/creatinine ratio will be evaluated from the first morning urine samples to assess albuminuria. Urinary albumin and creatinine concentrations will be determined using Wiener kits using the CMD-800 (Wiener Laboratories, Rosario, Argentina).

Blood samples will be taken after a 12-hour fasting period. Blood biochemical parameters will be performed by means of urea, creatinine, uric acid, triglycerides, total cholesterol, high-density lipoprotein cholesterol, low-density lipoprotein cholesterol, as well as, fasting glucose, basal insulin, and glycated hemoglobin will be evaluated. Other parameters will be evaluated, such as serum concentrations of total proteins, albumin, total calcium, phosphorus, sodium, potassium, magnesium, total alkaline phosphatase activity, parathyroid hormone (PTH), 25-hydroxyvitamin D [25(OH)D] and tacrolimus concentrations.

The urea, creatinine, uric acid, triglycerides, total cholesterol, high-density lipoprotein cholesterol, low-density lipoprotein cholesterol, fasting glucose, glycated hemoglobin, total proteins, albumin, total calcium, phosphorus, sodium, potassium, magnesium, total alkaline phosphatase will be evaluated in blood samples using *Wiener* kits according to the methodology described by the manufacturer, using the *CMD-800* biochemical analyzer (*Wiener Laboratories*, *Rosario*, *Argentina*). Further, PTH, 25(OH)D, basal insulin and tacrolimus concentrations will be measured by the chemiluminescence method with ABBOTT^®^ kits, using the ARCHITECT i2000SR Immunoassay *Analyzer (ABBOTT Diagnostics*, *Illinois*, *USA*).

All biochemical analyzes will be performed at all the time points in the study (T0, T3, T6, T9, and T12 after KTx).

### Assessment of dietary intake

Dietary intake will be assessed using the 3-day food record method completed by the patient himself, if literate, or by a caregiver who follows their daily routine, for 3 consecutive days that include a weekend day. Information about the food consumed, the amount and details of the type of the preparation, the times and places of meals, and the consumption of vitamin, mineral, and food supplements, will be collected. In periods T0, T3, T6, T9, and T12 after KTx, all the patients will be instructed on how to fill in the requested information and, to facilitate collection, all of them will receive a manual of home measurements prepared by the authors with images of utensils and conventional measures of food. The 3-day food record annotation form was adapted to facilitate the filling of meal-related information, by including information in a “step by step” form for a better understanding by patients or companions (S1 Appendix).

The analysis of the food records will be made in a qualitative way by observing the type and quality of the food consumed. The quantity of each food item and drink will be converted into grams or milliliters using a measurement chart for food consumed in Brazil. The foods will be converted into energy and nutrients using the Virtual Nutri Plus^®^ 2.0 (São Paulo, Brazil). Nutritional information from industrial food labels will also be included in the software database, as necessary, along with their nutrient composition obtained from the Brazilian food composition tables and the United States Department of Agriculture database, as appropriate [22–25]. For each patient, the average consumption of the 3 days will be considered in all the evaluated components.

### Anthropometric and body composition assessments

Anthropometric measurements such as weight, height, waist circumference (WC), and handgrip strength (HGS) will be collected. The current weight will be obtained using a digital platform scale from *Balmak*^®^ (São Paulo, Brazil), calibrated with accuracy class III, with a minimum capacity of 1 kg, and a maximum capacity of 150 kg. Height will be measured using an anodized aluminum stadiometer with a rectangular cursor from *Sanny*^®^ (São Paulo, Brazil), with wall-fixation with screws, a scale from 50 to 211 cm, and a resolution of 0.1 cm. To measure the WC, an inelastic measuring tape from *Sanny*^®^ (São Paulo, Brazil), with an extension of 200 cm and an accuracy of 1 mm will be used. The HGS, used to verify a reduction in muscle function, will be assessed based on the measurement of isomeric contraction of the hand muscles through an analog manual dynamometer from *Crown*^®^, with a scale from 0 to 100 kg and a resolution of 1 kg. The measurement will be conducted in triplicates, with the highest value being adopted between repetitions.

Body composition will be assessed at T0, T6, and T12 months after KTx using the *double-beam X-ray absorptiometry (DXA)* method, performed by the *LUNAR-GE*^®^ device *(Lunar Radiation Corporation*, *USA)*. For this, the measurements of lean mass (LM% and LM Kg), fat mass (FM% and FM/kg), body fat (%BF), bone mineral content (BMC), and fat-free mass (Kg) will be conducted.

### Assessment of the presence of sarcopenia

The presence of sarcopenia will be assessed through the recommendations of the European Group Working Sarcopenia Older People (*EGWSOP)* [26], considering the HGS data, to assess muscle mass function and body composition using DXA, verified by the Appendicular Muscle Mass Index (AMMI), to assess muscle mass.

### Quality of life assessment and physical activity

Participants in the case and control groups will be assessed for quality of life, using the generic questionnaire *Medical Outcomes Study 36-Item Short-Form Health Survey (SF-36)* translated and validated into Portuguese and applied in three periods T0, T6, and T12 after KTx [27]. The instrument consists of 36 items or questions, encompassed in eight domains and summarized into physical and mental components. The score for each domain ranges from 0 (worst health) to 100 (best health). The data analysis for tabulation will be performed through registration on an online platform through the website *qualipes*.*com*.*br* [38] by the same evaluator in all the stages of the study.

Considering that depression, anxiety, and other mental disorders can directly affect the quality of life of individuals, an interview will be conducted with the *Self-Reporting Questionnaire (SRQ-20)* [28], which is the Brazilian version of a psychiatric screening questionnaire that assesses non-psychotic mental disorders in the primary health care system, consisting of 20 items that can be answered as “Yes” or “No” with scores ranging between 7 and 8 points for men and women, respectively.

In addition to the previous parameters, the levels of physical activity of the patients will be assessed using the full version of the *International Physical Activity Questionnaire (IPAQ)*, translated and validated in Portuguese [29]. The IPAQ considers the activities carried out in the last seven days under four domains: means of transport, housework and recreation, sports, and leisure. The final score will be converted to MET-minutes/week. Assessment of physical activity will always be carried out by the same evaluator.

